## Abstract

**Background:**

There is an urgent need to develop and evaluate weight management interventions to address childhood obesity. Recent research suggests that interventions designed for parents exclusively, which have been named *parents as agents of change* (PAC) approaches, have yielded positive outcomes for managing pediatric obesity. To date, no research has combined a PAC intervention approach with cognitive behavioural therapy (CBT) to examine whether these combined elements enhance intervention effectiveness. This paper describes the protocol our team is using to examine two PAC-based interventions for pediatric weight management. We hypothesize that children with obesity whose parents complete a CBT-based PAC intervention will achieve greater reductions in adiposity and improvements in cardiometabolic risk factors, lifestyle behaviours, and psychosocial outcomes than children whose parents complete a psycho-education-based PAC intervention (PEP).

**Methods/Design:**

This study is a pragmatic, two-armed, parallel, single-blinded, superiority, randomized clinical trial. The primary objective is to examine the differential effects of a CBT-based PAC *vs* PEP-based PAC intervention on children’s BMI z-score (primary outcome). Secondary objectives are to assess intervention-mediated changes in cardiometabolic, lifestyle, and psychosocial variables in children and parents. Both interventions are similar in frequency of contact, session duration, group facilitation, lifestyle behaviour goals, and educational content. However, the interventions differ insofar as the CBT-based intervention incorporates theory-based concepts to help parents link their thoughts, feelings, and behaviours; these cognitive activities are enabled by group leaders who possess formal training in CBT. Mothers and fathers of children (8–12 years of age; BMI ≥85^th^ percentile) are eligible to participate if they are proficient in English (written and spoken) and agree for at least one parent to attend group-based sessions on a weekly basis. Anthropometry, cardiometabolic risk factors, lifestyle behaviours, and psychosocial health of children and parents are assessed at pre-intervention, post-intervention, 6-, and 12-months follow-up.

**Discussion:**

This study is designed to extend findings from earlier efficacy studies and provide data on the effect of a CBT-based PAC intervention for managing pediatric obesity in a real-world*,* outpatient clinical setting.

**Trial Registration:**

ClinicalTrials.gov identifier: NCT01267097

## Background

Pediatric obesity has increased dramatically in economically developed countries over the past several decades [1]. The most recent national estimates from the Canadian Community Health Survey revealed that 26% of Canadian children and youth were overweight while 8% were obese [2]. These data showed overweight and obesity increased 50% and 167%, respectively, since measured height and weight data were last collected from Canadian children in the late 1970s. This is an alarming trend since a high level of body fat in children and youth is linked to numerous adverse health outcomes including high blood pressure, dyslipidemia, insulin resistance, and non-alcoholic fatty liver disease [3]. In addition to the high proportion of boys and girls impacted by obesity-related medical co-morbidities, the psychosocial consequences of having an unhealthy weight are likely most salient for families. A number of reports have studied the connections between pediatric obesity and depression [4,5], anxiety [5], self-esteem [6], body image [7], executive functioning [8], as well as bias and stigmatization [9,10]. Collectively, this body of evidence highlights the variety of factors that influence the health and well-being of children with obesity.

There have been numerous calls for the development and evaluation of pediatric weight management interventions [11-13]. Such interventions are usually designed to improve lifestyle behaviours to reduce adiposity and risk factors for chronic diseases including type 2 diabetes and cardiovascular disease. Though researchers outside of Canada have established fundamental features of pediatric weight management, their application in a Canadian context has been limited. The Canadian Obesity Clinical Practice Guidelines (CPG) reinforced this knowledge gap [11]; notably, of all the weight management research used to inform the CPG, none of the evidence was Canadian. This situation is undesirable since Canada’s cultural, social, geographic, and health services uniqueness suggests that weight management interventions that work in other countries may not translate universally or successfully [14,15]. Despite these issues, a common theme underscored in almost every published report on pediatric weight management is the central role played by parents [16,17].

Parents play an invaluable role in creating a supportive home environment to enable their children to make healthy lifestyle choices [18,19]. Parents also serve as important role models given that parental attitudes and behaviours regarding physical activity and nutrition can have a substantial impact, both positively and negatively, on the attitudes and behaviours of their children [20-24]. Parenting style is also an important factor that impacts child health outcomes. In research extending Baumrind’s classical descriptions of parenting styles [25], children of parents who demonstrate controlling, restrictive behaviours exhibit less healthy dietary behaviours and are at increased risk of obesity *versus* children of parents who demonstrate more supportive, authoritative practices [26-30]. In addition, data on psychosocial stress within families suggests that improving the family system and parent–child relationships may reduce the risk of pediatric obesity [31]. Taken together, these observations support the need for weight management interventions that attend to both cognitive and behavioural factors within the family context.

The key role played by parents in pediatric weight management interventions was established in the early 1980s by the formative research conducted by Leonard Epstein and colleagues [28,32-35]. Their work has been extended in recent years through research focused on parents as agents of change (PAC) in lieu of treating parents and children as a dyad. Intervening with parents exclusively to address other health concerns in children and youth has been applied successfully in the past [36-38], but represents a newer model for care for pediatric weight management. If parent-only interventions are as effective as interventions that include children only or parent–child dyads, a parent-only model would be the most efficient (and likely cost-effective) treatment option. Indeed, emerging evidence supports a PAC treatment approach. For instance, in a randomized, one-year study of obese 6 – 11 year olds, [Golan et al. 39] compared two weight management interventions (one for children exclusively *versus* one for parents exclusively). While children in both groups lost weight, the reduction in percent overweight was greater for children in the parent-only group compared to those in the group that included children exclusively; program adherence and retention were also superior in the parent-only group. More recently, Golan and colleagues compared child weight loss in parent-only *versus* parent + child groups. Obese children of parents in the parent-only group showed greater reductions in adiposity compared to children in the parent + child group, improvements that were maintained at 18-months follow-up [40]. Since these initial reports, data from larger, higher-quality clinical trials have confirmed the beneficial effects of PAC interventions in pediatric weight management [41-44].

Though the aforementioned data have highlighted the fundamental leadership role parents can play in helping their children to achieve success in pediatric weight management, the interventions have provided limited insight into how and why the interventions promote behavioural and cognitive changes [45]. The current study builds on the seminal work of Golan and colleagues by applying a PAC approach, which includes a theoretically-based, clinical treatment modality (cognitive behavioural therapy, CBT) in comparison to the traditional psycho-educational approach that helps to interpret study outcomes. Although CBT has been used previously for treating pediatric obesity [46,47], our study addresses family-oriented issues with parents exclusively rather than focusing on boys and girls themselves. We believe that working with parents on their own may also allay concerns regarding intervening with children (i.e., stigmatization, low motivation, a lack of identifying obesity as a health concern). Further, by evaluating a PAC CBT-based intervention in an out-patient clinical setting in our local children’s hospital, the current trial is designed to expand on the promising findings from efficacy-based studies to determine the effectiveness of PAC interventions in a real-world environment, which often includes children with severe obesity. This paper describes the protocol our team is using to examine two PAC-based interventions for pediatric weight management. We hypothesize that children whose parents complete the CBT-based PAC intervention will achieve greater reductions in adiposity, improved lifestyle behaviours and psychosocial outcomes, and decreased cardiometabolic risk factors compared to children whose parents complete a psycho-education-based (PEP) PAC intervention, which is similar in content and structure to the CBT-based version, but does not include elements of cognitive behavioural therapy.

## Methods/Design

This study is a pragmatic, two-arm, parallel, single-blinded, superiority randomized clinical trial. The primary objective is to examine the differential effects of CBT-based PAC *vs* PEP-based PAC on children’s BMI z-score (primary outcome). Secondary objectives are to examine intervention-mediated changes in metabolic, behavioural, and psychosocial variables in children and parents. The RCT is conducted at the Pediatric Centre for Weight and Health (PCWH), which is an outpatient pediatric weight management clinic at the Stollery Children’s Hospital (Alberta Health Services) in Edmonton, Alberta, Canada. As a clinical program that offers weight management care to boys and girls with obesity (and their families), we have used different study designs to evaluate weight management interventions in the past, which has included applying a wait-list control group [48]. However, based on our team’s collective clinical and research experience, a study design that includes offering health services to families as close as possible to their entry into our clinic satisfies our institutional commitment to provide timely access to weight management health services. With this in mind, developing and comparing two PAC interventions (CBT and PEP) that are similar but distinct meets our academic aim to compare the effectiveness of two evidence-informed approaches [49].

### Ethical considerations

The PAC RCT is registered with ClinicalTrials.gov (NCT01267097) and has received approval from both the Human Research Ethics Board (University of Alberta) and the Northern Alberta Clinical Trials and Research Centre. Family recruitment is conducted by a research coordinator within our weight management clinic. Informed and written consent and assent are obtained from parents and children, respectively, at the point of recruitment. Families who are referred to our weight management clinic and satisfy our inclusion criteria, but decline participation, still receive weight management health services, so no families are refused care. In recognition of families’ time and effort, tokens of appreciation (i.e., gift cards to a local shopping centre) are offered to families at each data collection time point (pre-intervention, post-intervention, 6- and 12-months follow-up).

### Recruitment

Families are eligible for this study if (*i*) children are between 8 – 12 years old, (*ii*) children present with an age- and sex-specific BMI ≥85^th^ percentile [50], (*iii*) at least one parent agrees to attend weekly PAC sessions for 16 weeks, and (*iv*) children and parents are fluent in English (verbal and written). Recruitment is conducted primarily through the PCWH, although we also attempt to recruit families from the greater Edmonton area through advertisements (e.g., posters on local health, community, and recreation centers, mail outs to local family and pediatric medical clinics).

### Timeframe

Data are collected from families at pre-intervention, post-intervention, 6-, and 12-months follow-up. For practical reasons, at each time point, data collection occurs within a 2-month window (e.g., within 8 weeks before the first PAC session, within 8 weeks after the last PAC session, and between 4 weeks before to 4 weeks after each of the 6- and 12-month follow-up time points). Clinical and research experience by our team [48] revealed that this timeframe is needed to accommodate families’ schedules and clinical capacity to complete data collection, which also differentiates our real-world, comparative effectiveness research [51] from more stringent criteria that are applied in the context of efficacy studies. Data collection is completed by clinicians working within the PCWH, and given the real-world, applied health services environment within which the study is conducted, we are unable to blind them from knowing which families are receiving the CBT- and PEP-based versions of the PAC intervention [52].

### The PAC interventions: design and delivery

The PAC curriculum (please see Table 1) was developed using strategies consistent with intervention mapping [53] by incorporating evidence-based, lifestyle and behavioural strategies for pediatric weight management [54]. Both the CBT and PEP interventions consist of 16 weekly sessions that are offered to parents (in the evening) twice yearly (September – December; January – April). Sessions are held within our health care institution in classrooms within different areas of the hospital as a means to minimize cross-group contamination. Two healthcare professionals (e.g., dietitian, nurse, fitness professional, mental health professional) per intervention arm provide the curriculum to small groups of parents that will range in size to no more than 15 parents/group. Although at least one parent per family is required to attend the group sessions, additional parents or caregivers are welcome.

**Table 1 T1:** An overview of the Parents as Agents of Change (PAC) intervention curriculum

**Session**	**Title**	**Content overview**
1	*Welcome*	Introduction and orientation; parents receive pre-intervention snapshot of their children’s lifestyle, behavioural and metabolic health measurements, which is used throughout the intervention to inform decisions regarding behaviour change priorities and goal-setting
2	*Food For Thought*	Canada’s Food Guide, PAC nutrition goal #1 (intake of vegetables and fruit)
3	*More Food For Thought*	Canada’s Food Guide, PAC nutrition goals #2 (intake of whole grain products) and #3 (intake of sugar-sweetened beverages)
4	*It’s Your Move*	Canada’s Physical Activity Guide for Children, PAC physical activity goal #1 (steps / day)
5	*Screensavers*	Canada’s Physical Activity Guide for Children, PAC physical activity goal #2 (leisure time screen time)
6	*Portion Distortion*	Food labels, serving sizes *vs* portion sizes
7	*Move It!*	Canada’s Physical Activity Guide for Children, PAC physical activity goal #3 (moderate-to-vigorous physical activity)
8	*Staying On Track*	Behaviour change relapse prevention
9	*Get A Cue!*	Social cues influencing nutrition and physical activity
10	*Positive Parenting Partnerships*	Limit-setting, boundaries, communication
11	*Community Connections*	Environmental factors influencing nutrition, physical activity
12	*Eating Out, Eating Healthy*	Menu reading, providing healthy lunches
13	*Feelin’ Groovy!*	Healthy self-esteem and body image
14	*Time Management*	Family-based priority setting
15	*He Said, She Said*	Bullying, sibling rivalry, peer relationships
16	*Ready, Set, Go!*	Intervention review, future planning and goal-setting

The PAC intervention includes a variety of different educational approaches such as didactic teaching, individual/private parent activities, group-based brain-storming/problem-solving, and inter-active experiential learning. The intervention content is presented to parents through a *PowerPoint*® slide set; as group leaders deliver the manualized content, parents follow along with their individual parent manuals (please see Additional file 1: Appendix for sample content from both leader and parent manuals). Leader manuals include the individual slides, information to be presented to the group, description of the aforementioned learning activities for parents, and a list of references (i.e., journal articles, books) that were used to develop the curriculum. Parent manuals include a copy of the slides, descriptions of the intervention activities, and lined spaces for parents to record notes and complete goal-setting activities on a week-by-week basis. Additional information (i.e., educational handouts, local resources) is made available for parents within the classroom on a community resource table. In lieu of potentially overloading parents with information related to nutrition, physical activity, behaviour change, and local resources for families, a decision was made by our team during the intervention development phase to limit the curriculum to what we viewed as ‘need to know’ information that was directly related to pediatric weight management. Information on topics that are team considered was ‘nice to know’ was removed from the curriculum and provided to families on the community resource table, which is intended to provide parents with optional information that parents may find interesting and relevant, but is not central to pediatric weight management and integral to helping families make healthy behaviour changes.

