#### Physical activity and sedentary behaviours

Children and parents measure prospectively their total physical activity using a pedometer (Yamax Digi-Walker SW-200) over a 7-day interval that overlaps with their dietary intake recording. Families receive training on proper pedometer positioning, data recording, and other physical activity monitoring details before the measurement interval starts. To ensure proper functioning, all pedometers are calibrated prior to use by way of a standardized step count test. Since pedometers do not capture information regarding physical activity intensity, children and parents complete simultaneously a 7-day physical activity record to document quality, quantity, and patterns of moderate-to-vigorous physical activity, leisure-time screen time (television, computer, video game, etc.), and sleep duration. Once records are returned, data are reviewed with families to ensure completeness and clarify durations and intensities of activities.

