### Statistical analysis

Data cleaning, analyses, figures, tables, and statistical sections for dissemination are conducted by a blinded biostatistician with the Biostatistics Consulting Group within the Women and Children’s Health Research Institute (http://www.wchri.org) at the University of Alberta. Spotfire S + 8.2 (TIBCO Software Inc, 2010) and SAS 9.3 (SAS Institute Inc, 2010) will be used for analyses. Analyses are conducted both with PAC intervention completers only and with all participants (to evaluate effectiveness). Continuous variables are described by summaries (e.g., means, medians, ranges and SDs) and frequency distributions are determined for categorical variables. For the primary and secondary outcome variables, the percent change from pre- to post-intervention (as well as 6- and 12-months follow-up) for both groups is determined and summarized along with the 95% confidence intervals (CIs) for mean percent change. Boxplots and histograms are used to display the percent change for these variables; bar charts are used for categorical variables. Our analyses are conducted separately for each mean percent change at each observation time (i.e., pre-intervention to post-intervention, pre-intervention to 6-month follow-up, and pre-intervention to 12-month follow-up). Statistical tests are set at conventional levels (p < 0.05) and all analyses are intention-to-treat. Multiple imputation methods may be used in the event of missing data. To minimize the risk of bias, a research team member with no direct contact with enrolled families is leading the data analyses.

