To compare interventions, one-sided independent samples Student’s t-test assesses percent changes in BMI z-score (primary objective); if required, data transformations are used to ensure data normality. A similar process is used to determine intervention-mediated changes in other physiological, behavioural, and psychosocial outcomes (secondary objectives). In addition, the percentage of families with improved categorical outcomes (i.e., those who do/do not meet recommendations from *Eating Healthy with Canada’s Food Guide*) is compared across interventions using a one-sided independent samples proportion tests. A multivariable linear regression model is developed for the primary outcome (percent change in BMI z-score) to determine the intervention group effect while controlling for potential confounders (i.e., cohort, percent attendance, household income). If any of the intervention groups include siblings, CIs are adjusted using variance inflation factors, and univariable or multivariable random intercept mixed effects models are used in lieu of Student’s t-tests and multivariable linear regression, respectively. Analogous calculations are made to compare the percent change from pre-intervention to 12-month follow-up, although intervention attrition may reduce our power to detect a significant difference. Mixed effect models are developed to examine the effects of the interventions on primary and secondary outcomes over time. This approach allows all pre-intervention, post-intervention, and follow-up data to be included in our modeling. For all models, residual diagnostics are used to assess model assumptions and appropriate transformations and/or non-linear terms are included as necessary. Our reporting of study results is in accordance with the CONSORT statement [91].

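### Pre and post activity records fall in opposite seasons for the two yearly courses, yet the stated test for these secondary outcomes carries no cohort term

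*Protocol article*

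**What the plan says.** - **Calendar.** The section on design and delivery of the interventions describes "16 weekly sessions that are offered to parents (in the evening) twice yearly (September – December; January – April").
- **Windows.** The Timeframe section places the first two assessments "within 8 weeks before the first PAC session, within 8 weeks after the last PAC session".
- **Measures.** The section on physical activity and sedentary behaviours states: "Children and parents measure prospectively their total physical activity using a pedometer". The count covers seven days. A seven-day record of moderate-to-vigorous activity (MVPA), screen time and sleep is kept alongside it. The single site is in Edmonton.
- **Per-arm summary.** The Statistical analysis section says that percent change "for both groups is determined and summarized along with the 95% confidence intervals (CIs) for mean percent change".
- **Test.** The primary comparison is a one-sided two-sample t-test on percent change. The same section continues: "A similar process is used to determine intervention-mediated changes in other physiological, behavioural, and psychosocial outcomes (secondary objectives").
- **Adjustment.** A regression controlling for cohort, percent attendance and household income is stated for percent change in BMI z-score only. Mixed models are planned for primary and secondary outcomes, and their terms are not listed.

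Season is not mentioned in the document.

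**The concern.** A one-week step count or screen-time record is a free-living measure and could well depend on the time of year. Under this calendar the pre-to-post change carries a seasonal component, with one sign for September courses and the other for January courses. Pooling them has two effects.

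First, the opposite shifts enter the within-arm spread of percent change. A t-test that ignores cohort counts that spread as noise.

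Second, an arm's own mean change includes whatever part of the seasonal shift does not cancel. Neither arm is untreated, and the article says that the psycho-education arm is not a true control. Nothing in the trial can therefore separate season from programme effect within an arm.

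The investigators recognise cohort as a covariate, but apply it to BMI z-score and not to the activity records, where a seasonal effect is more plausible.

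**Working it through.** **The plan's own figures.** The document gives no seasonal figure and no power statement for any lifestyle outcome. Its 80% power statement for the two-arm comparison concerns BMI z-score and is not used here. Only the expected 30 analysed families per arm and the one-sided 0.05 level are taken from it.

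**Step 1: dates.** Sixteen weekly sessions span 15 weeks. Start dates of 6-15 September and 4-15 January are illustrative.

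| Course | Pre window | Post window |
|---|---|---|
| September | mid-July to mid-September | about 20 December to 23 February |
| January | about 9 November to 15 January | about 18 April to 24 June |

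The window midpoints are 4 + 15 + 4 = 23 weeks apart, with a possible range of 15 to 31 weeks. The September course moves from summer to winter, the January course from early winter to spring.

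**Step 2: assumptions.** None of these is in the documents.
- Season shifts percent change by −s in September courses and +s in January courses, with s = 10, 20 or 25 percentage points.
- The SD of percent change within a course is 30 or 40 points.
- The September share is p = 2/3. At most 15 parents per group and 45 families per arm mean at least three groups per arm. Three equal groups, one per course, give a 2:1 mix in one direction or the other.
- Cohorts are balanced across arms, as block randomisation adopted because of cohort enrolment should roughly achieve.

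**Step 3: arm difference.** Both arms receive the same mix of shifts, so season cancels from the difference. Its true standard error stays at SD × √(2/30), which is 7.7 at SD 30 and 10.3 at SD 40, whatever s is.

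**Step 4: estimated standard error.** The pooled variance is inflated by V = 1 + 4p(1−p)s²/SD² = 1 + (8/9)s²/SD². The estimated standard error is therefore about √V times too large.

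**Step 5: power.** The benchmark is an effect of 0.65 SD, which has 80% power at 30 per arm with no seasonal shift. Its noncentrality is 0.65 × √15 = 2.517, and the critical value on 58 degrees of freedom is 1.672. Approximate power is Φ(2.517 − 1.672√V), and approximate type I error is 1 − Φ(1.672√V).

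| s | SD | V | √V | Power | Type I error |
|---|---|---|---|---|---|
| 10 | 30 | 1.099 | 1.048 | 78% | 4.0% |
| 10 | 40 | 1.056 | 1.027 | 79% | 4.3% |
| 20 | 30 | 1.395 | 1.181 | 71% | 2.4% |
| 20 | 40 | 1.222 | 1.106 | 75% | 3.2% |
| 25 | 30 | 1.617 | 1.272 | 65% | 1.7% |
| 25 | 40 | 1.347 | 1.161 | 72% | 2.6% |

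Simulation of the same settings agrees within about one percentage point. A linear model with arm and cohort gave power of about 80% and type I error of about 5% in every row.

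**Step 6: an arm's own mean.** The residual shift is (1−p)s − ps = −(2p−1)s. At p = 2/3 this is −s/3, or about −3 to −8 points for s = 10 to 25. At p = 1/2 with equal swings it is zero. With more January families the sign reverses.

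**The case against.** The strongest reply is that the trial exists to compare two programmes, and season does not bias that comparison. The unadjusted test errs on the conservative side, so it raises no false-positive concern. Every size input is assumed, and at a 10% swing the loss is only 1-2 points. All of this stands and limits the weight of the point.

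Several stronger readings are tempting but not supported:
- **The plan labels within-arm change as an intervention effect.** A reader might infer this from the phrase about intervention-mediated changes. In the Statistical analysis section that sentence follows directly on the between-arm t-test and most naturally refers to it. The per-arm percent changes are given as summaries. The need is to keep them descriptive; the plan has not made a false claim.
- **Sixty families carry the information of about 43-49.** Dividing 60 by V at a 20% swing gives these figures (60/1.395 and 60/1.222). That treats course mix as varying independently between arms. With cohorts balanced by blocking, the arm difference is no noisier and only its estimated standard error is too large.
- **Each arm's change is off by 3-8 points.** This depends on the 2:1 mix, and the document does not fix the mix.
- **The 6- and 12-month profile alternates season.** The Timeframe section does not say whether these visits are counted from baseline or from course end.
- **The mixed models omit season.** Their terms may properly be left to a fuller analysis plan.

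The explicit choice remains: secondary outcomes follow an unadjusted t-test, while cohort is named for the primary outcome alone.

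**Conclusion.** The point holds as one of efficiency and interpretation for step count, MVPA and screen time. That pre and post records sit in different seasons, in opposite directions for the two courses, follows from the stated dates. Whether this matters depends on how far activity varies by season in this population, which the documents do not say. Under the assumptions listed, the cost is negligible at a 10% swing and becomes material at about 20%, where power drops from 80% to 71-75% and the actual type I error to about 2-3%. The within-arm effect ranges from zero at an equal course mix with equal swings to about a third of the swing at 2:1. There is no bias in the randomised contrast, and the point does not concern the primary outcome. It is minor to moderate.

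**What to change.** For step count, MVPA and screen time:
1. Replace the unadjusted t-test with a linear model containing arm and cohort.
2. Carry cohort, with a visit-by-cohort term, into the mixed models for these outcomes, so that the arm effect at each visit is estimated within cohort.
3. Present per-arm pre-to-post change as descriptive, or separately by course, and do not interpret it as an intervention effect.

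Cohort is already recorded and already used for the primary outcome, so no new data or visits are needed. The cost is a few degrees of freedom and more modest within-arm statements.
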